### Interventions

#### Residential TAU

TAU consists of the standard residential services offered to adolescents at our partner facility and will be received by families in both conditions. The partner residential treatment program, Rosecrance Health Network, offers residential treatment for adolescents at two locations, one in Rockville, Illinois, and one in Sioux City, Iowa. Length of stay ranges from 2 to 45 days, depending on the adolescent’s level of need and insurance coverage. Adolescents at Rosecrance Health Network receive about 15 hours of educational programming and 25 hours of treatment per week in a predominantly group-therapy model based on dialectical behavioral therapy [30]. Each adolescent is also assigned a primary counselor who checks in with them at least twice per week. Medication management is offered by a nurse practitioner or psychiatrist as needed. Prior to discharge, parents receive standard discharge planning, which consists of a customized relapse prevention plan as well as either a referral to a new outpatient therapy provider or a return to a prior outpatient therapy provider. Families receive referrals to a psychiatrist or local self-help group as indicated. Postdischarge, families are encouraged to phone the intake coordinator for further referrals or support.

Following randomization, parents will be given an educational pamphlet about adolescent substance use, parenting skills, and local community resources, consistent with usual resource provision at the partner site.

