We previously tested the Parent SMART intervention via a pilot randomized controlled trial with 61 parent-adolescent dyads across two residential programs (one acute care and one standard residential care) [27]. Results of the pilot trial met or exceeded all of the recruitment, retention, acceptability, feasibility, and fidelity benchmarks established a priori as evidence that the intervention was worthy of further study in a larger trial. Parent SMART demonstrated excellent acceptability and feasibility, with parents who received Parent SMART reporting significantly higher levels of satisfaction and greater likelihood of recommending the services they had received than those who received residential treatment alone [27]. In addition, Parent SMART was associated with significant improvements in parental monitoring and communication, measured via both self-report scales and a behavioral intervention task, across both residential settings [28]. Among adolescents in the acute care setting, Parent SMART was also associated with significant reductions in days of binge drinking and school-related problems; we were underpowered to detect differences in the standard residential care setting, but a number of significant time effects were observed, revealing encouraging reductions in days of substance use, substance-related problems, and high-risk behaviors among adolescents in both conditions [27]. Building upon this prior work, the current protocol describes a fully-powered, randomized controlled trial testing the effectiveness of Parent SMART as an adjunct to residential TAU on parenting skills, adolescent substance use, and problems commonly related to substance use such as school truancy, externalizing behavior, sexual risk behavior, and criminal involvement [10]. A conceptual overview of the study’s specific aims is presented visually (Figure 1) and elaborated upon as follows.

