## Methods

### Study Design and Ethical Considerations

Parent-adolescent dyads will be assigned to receive either residential TAU or Parent SMART+ residential TAU on a 1:1 schedule using a two-arm, parallel-group, randomized trial design. The Brown University Institutional Review Board has approved all study procedures described herein (ID# 2006002748). The study is registered in clinicaltrials.gov (NCT05169385). The timing of key study elements, including randomization and parent-adolescent assessments, is depicted in Table 1.

**Table 1 table1:** Timing of key protocol elements.

		Residential treatment					Postdischarge period		
Timepoint		Enrollment	Baseline assessment	Allocation	Residential stay (2-45 Days)	6 weeks		12 weeks	24 weeks

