### Randomization

Parent-adolescent dyads will be randomized immediately after completing the baseline assessment using the urn randomization method [29], which systematically biases randomization in favor of balance across conditions. Dyad randomization will be balanced according to adolescent biological sex at birth (male vs female), planned length of stay in residential (0-10 days vs 10+ days), and parent’s preferred language (English vs Spanish). Random assignments will be made using an Excel urn generator developed by Stout and colleagues for Project MATCH [22]. Parents will be informed about their treatment assignment shortly after randomization. Residential staff and study research staff conducting follow-up assessments will be blind to the condition.

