##### Covariates: Demographics

Parent and adolescent sociodemographics will be assessed and controlled for as covariates. Parents will complete a routine sociodemographic form. Adolescents will complete the GAIN Background section, which collects routine sociodemographic variables including age, sex, gender identity, ethnicity, race, and grade in school. Items in other GAIN sections indicate the adolescent’s history of substance use or mental health treatment utilization, data that will be used to control for treatment received.

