#### Power

The study’s primary and secondary aims were specifically powered to detect small to medium effect sizes on the Time*Condition interactions, based on: (1) the effect sizes detected in our pilot trial, which were small to medium in size, and which matched the proposed population in terms of severity; and (2) the effect sizes of the online parenting program on parenting processes detected in prior clinical trials, which were medium to large [24,32,33]. With a sample size of 220 dyads, we will have 80% power to detect a 0.38 standard deviation effect size or larger with a type I error risk of .05.

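### Randomization is not balanced on residential location, and no covariate the article names is location, so a small gain in precision and balance is given up

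*Protocol article*

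**What the plan says.** The Residential TAU section says that the partner network treats adolescents at two residential locations, "one in Rockville, Illinois, and one in Sioux City, Iowa". Usual care is the comparator and is also the base of the experimental arm. The section describes several parts of it as local or individual to the family: referral to an outpatient provider, referral to a psychiatrist or nearby self-help group, and a pamphlet that covers community resources.

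The Study Design section allocates dyads "on a 1:1 schedule using a two-arm, parallel-group, randomized trial design". The Randomization section then names the urn factors: "Dyad randomization will be balanced according to adolescent biological sex at birth (male vs female), planned length of stay" (0-10 versus 10+ days), followed by the parent's preferred language. The list has three factors and reads as complete. Location is not in it.

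Covariates appear in three places. The Covariates section says "Parent and adolescent sociodemographics will be assessed and controlled for as covariates" and adds treatment history from the GAIN. The Data Analysis Plan overview and the limitations paragraph of the Discussion add contact time. None of these names location, and the latent change score models are described without a location term. The article gives no expected enrolment split between the two locations.

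**The concern.** Each dyad's location is known before randomization and costs nothing to record. The outcomes are measured 6 to 24 weeks after discharge, when families rely on aftercare in their own area. Location is therefore a reasonable candidate to predict how outcomes change after discharge, even though the article reports no such difference.

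If it does predict change, two things follow from an allocation and an analysis that both ignore it. The part of the variance due to location stays in the residual, so the treatment effect is estimated slightly less precisely than it could be. And if the arms happen to differ in location mix, that particular trial's estimate moves by the imbalance times the location difference, with nothing in the named covariates to remove it. These are two views of the same loss of precision, not two separate harms.

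**Working it through.** **Inputs from the article.** 220 dyads, 1:1 allocation, hence 110 per arm. The Power section says: "we will have 80% power to detect a 0.38 standard deviation effect size or larger with a type I error risk of .05". Two locations.

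**Inputs assumed, because the article does not give them.** q, the share of dyads at one location: 0.5, with 0.2 as a sensitivity case. D, the difference between locations in outcome change, in units of the outcome SD: 0.1 to 0.5. Location is taken as independent of the three urn factors; if it is correlated with them, the imbalance below is somewhat smaller.

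**Step 1: reproduce the plan's figure.** For an unadjusted two-sample comparison at two-sided 5%, the detectable effect at 80% power is (1.960 + 0.842) × √(2/110) = 0.378 SD. Power at 0.38 SD is 80.5% (normal) or 80.1% (noncentral t). A one-sided test would give 88.0%, so the two-sided reading is the one that fits. The stated 80% is reproduced without any location term.

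**Step 2: chance imbalance.** When allocation ignores location, the arm difference in location share has SD √(q(1−q) × 2/110).
- q = 0.5: √(0.25 × 2/110) = 0.067, or 6.7 points. The 95% range is 1.96 × 6.7 ≈ ±13 points, and the chance of exceeding 10 points is 14%.
- q = 0.2: √(0.16 × 2/110) = 0.054, or 5.4 points. The 95% range is about ±11 points.

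**Step 3: effect on the estimate and on precision.** The shift in an unadjusted estimate is imbalance × D. With total SD set to 1, location explains R² = q(1−q)D². After adjustment the detectable effect is 0.378 × √(1−R²), and the gain is equivalent to 220 × R²/(1−R²) extra dyads. For q = 0.5 and an imbalance at the 95% limit (0.132):

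| D (assumed) | Shift, SD | R² | Detectable effect, SD | Power at 0.38 SD | Equivalent extra dyads |
|---|---|---|---|---|---|
| 0.1 | 0.013 | 0.0025 | 0.377 | 80.6% | 0.6 |
| 0.2 | 0.026 | 0.0100 | 0.376 | 80.9% | 2.2 |
| 0.3 | 0.040 | 0.0225 | 0.373 | 81.3% | 5.1 |
| 0.5 | 0.066 | 0.0625 | 0.366 | 82.9% | 14.7 |

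Unadjusted power is 0.8046. The gain runs from 0.8056 − 0.8046 = 0.001 to 0.8291 − 0.8046 = 0.0245, that is, about 0.1 to 2.5 points. The largest shift, 0.066 SD, is 0.066/0.38 ≈ 17% of the target effect.

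**Step 4: unequal enrolment.** At q = 0.2 the shift at the 95% limit is 0.011 to 0.053 SD over the same range of D, and adjusted power reaches at most 82.0%. As one location takes over enrolment, both quantities tend to zero.

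**The case against.** The strongest objection is that nothing the article states is wrong. Three urn factors are a legitimate choice, the power figure is reproduced, and randomization already allows for chance imbalance in the standard error. That is correct, and it limits the point to a small improvement.

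Three stronger readings are tempting and are not supported.

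- **That location is excluded from the models.** A reader might infer this from its absence among the named covariates. The article is condensed, the Covariates section mainly describes what the assessment forms collect, and a full covariate list may stand in an analysis plan that is not shown. Absence is shown only for the covariates named here. The urn is different: its factors are given as a complete list, and an analysis plan cannot add a randomization factor afterwards.
- **That the pilot showed outcomes to differ by site.** The Background section says of the pilot that "we were underpowered to detect differences in the standard residential care setting". Lack of power is not evidence of a difference. The pilot contrast was acute versus standard residential care, not Illinois versus Iowa, and the parenting improvements appeared in both settings.
- **That the treatment effect is biased or the type I error inflated.** Neither follows. Under randomization the imbalance averages to zero, and its variability is already counted in the unadjusted standard error.

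It is also fair to say that the article describes one network with one treatment model and refers to the partner facility in the singular. No difference between locations is documented. Modelling change from baseline largely removes stable location differences in level, which is why D above refers to differences in change. Balancing planned length of stay may absorb part of any location difference, but it does not address different aftercare communities.

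**Conclusion.** The point holds as a minor design improvement. Location is absent from a complete list of balancing factors and from every covariate the article names, so a chance imbalance is not prevented and, on what is stated, not corrected.

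Under an equal split and location differences in change of up to 0.5 SD, the price is at most about 2.5 points of power, with a shift in a single trial's estimate of up to about 0.07 SD at the edge of the 95% range of imbalance. At differences of 0.1 to 0.2 SD it is close to nothing. The split and the location differences are assumptions, and the loss disappears if only one location enrols. No conclusion of the trial depends on the point; it is worth acting on because the remedy is almost free.

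**What to change.** Add residential location as a fourth two-level urn factor. When the article was written, recruitment was scheduled but had not begun. Prespecify location as a fixed covariate in the primary and secondary models as well, unless the full analysis plan already does so, in which case confirming it settles that half. If enrolment has started and the urn can no longer be changed, the covariate alone still recovers the precision, provided it is fixed before unblinding. If only one location will enrol, saying so closes the point.

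The cost is one more column in the urn spreadsheet and one parameter per model (one for each change equation where changes are modelled separately). No new data are needed.

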#### Parent SMART

Parents randomized to Parent SMART will receive a technology-assisted intervention containing three core elements, which were packaged in response to formative feedback described extensively [26] and tested in the pilot trial [27,28]. All three elements are available in both English and Spanish.

##### Online Parent Skills Program

Parents will receive a 24-week subscription to an off-the-shelf, online parent skills program called Parenting Wisely (Figure 2) shortly after randomization to Parent SMART. Parenting Wisely (Ser Padres Con Sabiduría) is a self-administered, multimedia online program that has demonstrated effectiveness in reducing youth problem behavior across multiple independent studies [24,31-33]. The program contains nine modules, each of which corresponds with a common family problem (eg, finding drugs, monitoring of friends, sibling conflict, etc). Core skills emphasized across the Parenting Wisely modules include two communication skills (I-Statements and Reflective Listening) and two monitoring skills (Contracting and Asking Key Questions). The program also comes with a workbook that outlines all the vignettes, along with a glossary of terms, sample behavior charts, and practice exercises.

**Figure 2 figure2:**
[figure not shown]
Parenting Wisely computer program.

After selecting a module, parents are shown a video clip depicting a family struggling with that problem. Parents then select from three possible video vignette solutions, only one of which demonstrates an effective approach. Parents then receive feedback via video enactment of their chosen solution. The video enactment labels specific parenting skills, explains why the solution was either effective or ineffective and discusses how effective parenting skills (eg, monitoring and communication) can protect against common family problems.

The full Parenting Wisely program takes 3-5 hours to complete depending on user speed and depth of use. Parents will have a unique login, which will allow the research team to monitor their usage. In the pilot trial, 83% of the parents randomized to Parent SMART completed at least two modules, and 33% completed at least five modules. Overall, parents completed a mean of 3.8 modules (SD 2.3, range 1-9 completed modules) [28].

##### Networking Forum

Parents will also receive access to a networking forum containing two main channels (Ask an Expert and Connect with Parents) along with parenting resources, information about the study team, and customizable settings (Figure 3). The Ask an Expert channel allows parents to pose questions to a team of licensed clinical psychologists, whereas the Connect with Parents channel enables parents to pose questions and comments to other parents of adolescents in residential treatment. The networking forum will be accessible via smartphone app or web browser. The smartphone app will use push notifications to send a daily “Tip of the Day!” offering encouragement, reminders to use the forum, and/or links to Parenting Wisely videos; if the push notification is not opened, parents will receive the notification via SMS message two hours later. In the settings tab, parents can also subscribe to SMS notifications every time someone posts in one of the two main channels.

**Figure 3 figure3:**
[figure not shown]
Parent SMART (Substance Misuse in Adolescents in Residential Treatment) app interface.

The networking forum has been carefully designed so that parents can view all content (including push notifications and SMS messages) in either English or Spanish, using a mix of static content that is pretranslated (eg, page headings and team bios) and user-generated content that is translated via a Google translator set-in. Parents will select their preferred language in the forum’s user settings. A bilingual expert moderator will review and correct translation errors. This will allow Spanish-speaking parents to interact with posts by English-speaking parents in both forums and vice versa with minimal disruption. On an ongoing basis, the expert moderator will review all posts submitted to both channels to remove any potentially identifiable information or objectionable material.

Posts submitted to the Ask an Expert forum will be answered by a team of expert adolescent clinical psychologists to ensure continuous coverage. Responses to parent questions will follow a specific formula: validation of concern, reference to a specific Parenting Wisely core skill, and reference to a specific Parenting Wisely module(s) most relevant to the concern. By contrast, posts submitted to Connect with Parents will be viewed by other parents, who can “like” posts or provide comments.

In the pilot trial, 21 of the 30 parents (70%) randomized to Parent SMART posted a total of 16 times in Ask an Expert and 50 times in Connect with Parents. Qualitative analysis of the posts revealed five key themes: parenting skills, parent support, managing the transition home from residential care, adolescent substance use, and family functioning [34]. Parents will be told to expect replies within 24 hours; the average lag time in our pilot trial was 1 to 2 hours.

##### Coaching Sessions

Telehealth coaching sessions will be offered to support the customization of the content in the Parenting Wisely computer program and encourage engagement in the networking forum. Each session will consist of the rationale for a specific parenting skill, review of a Parenting Wisely module, practice applying the skill to a specific problem, and consideration of questions that the parent would like answered via the networking app. Focal parenting skills covered will align exactly with the Parenting Wisely skills to address parental monitoring (I-Statements and Reflective Listening) and communication (Contracting and Asking Key Questions). Parents will be asked to schedule sessions at times when they can access the internet to view Parenting Wisely modules. The initial 60-minute session will consist of an orientation to the Parenting Wisely program and networking app. Subsequent 45-minute sessions will follow the same basic outline without the orientation. When parents have questions or introduce problems/ concerns about their teen, the coach will first provide validation and then discuss how the parents’ problems can be addressed using a specific Parenting Wisely core skill. For homework, parents will be encouraged to complete Parenting Wisely modules that map onto their unique concerns (with reference to specific pages of the parent workbook for additional practice) and to use the networking forum to solicit feedback from either an expert or another parent.

In the pilot trial, 29 of the 30 parents randomized to Parent SMART initiated coaching sessions. On average, parents attended 2.7 coaching sessions, out of a maximum of 4 (SD 1.1, range 1-4) [27].

#### Parent SMART Coach Training, Fidelity and Competence

Parent SMART sessions will be delivered by BA-level or MA-level coaches, consistent with the approach used in the pilot trial. At least one counselor fluent in Spanish will be available at all times. A licensed clinical psychologist (protocol Principal Investigator), with expertise in training front-line community counselors, developed the training materials and will lead an initial 2-hour training. Prior to the training, coaches will be asked to review the Parent SMART manual, complete two modules in the online Parenting Wisely program, visit the parenting networking forum, and listen to two prerecorded coaching sessions that demonstrate all session elements. During the training session, coaches will conduct multiple role plays of the sessions to gain practice delivering the intervention content.

Before being assigned Parent SMART+TAU participants, each coach must submit two audio-recorded role plays that meet adherence and competence benchmarks. Counselor adherence to each Parent SMART session will be rated via study-specific adherence checklists that range from 0 (no elements covered) to 15 (all elements covered), with the target level of adherence set at 80% coverage. Competency will be rated via the well-validated 6-item “General Therapeutic Skills” subscale of the Cognitive Therapy Rating Scale [35,36]. Items will be scored on 6-point Likert scales ranging from 1 to 6 and then averaged; a mean score ≥4 will indicate competence. All sessions will be rated for adherence and competence by research staff trained in the rating process, with at least 25% of sessions double coded. A different licensed clinical psychologist (second author) will lead weekly supervision meetings with coaches, focused on tailoring sessions to address each family's unique presenting concerns.

A total of 78 sessions occurred in the pilot trial: all were rated on the coach’s adherence to protocol and competence by a single coder, and 33% were double coded. In total, 87% of sessions met the adherence, and 100% met the competence benchmark [27]. Agreement between coders was excellent: inter-rater reliability measured via the intraclass correlation coefficient was 0.92 for adherence and 0.86 for competence.

### Study Assessments

Parents and adolescents will complete a baseline assessment shortly after admission to the partner facility. Follow-ups will be conducted by research staff blind to condition at 6, 12, and 24 weeks postdischarge. The baseline assessment will be approximately 90-120 minutes for adolescents and 45-60 minutes for parents; each follow-up assessment will take approximately 60 minutes for adolescents and 30 minutes for parents. If a parent loses physical custody of the adolescent postdischarge, adolescent data will still be collected, and parent data will be classified as missing; administration of the full parent battery will be resumed if the parent regains physical custody. If an adolescent turns 18 over the course of the 24-week follow-up period, then the adolescent will be reconsented as an adult at the next relevant follow-up visit.

